### Planned Data analysis

#### Clinical Efficacy

All analyses will be conducted on an intention to treat basis by an investigator who is blind to group allocation. The outcomes measured at 4, 8, 12, 26 and 52 weeks will be used to generate efficacy and recurrence indices that will be analysed using linear mixed and logistic regression models [10]. Baseline scores for each dependent variable will be entered as a covariate, relevant participant characteristics entered as a random effect and treatment conditions and time as fixed factors. Variables such as age, gender, duration of condition, nature of employment will be included as covariates in the analysis, if found to significantly influence outcomes over time. Regression diagnostics will be used to check for normality of the measures and homogeneity of variance where appropriate. Alpha will be set at 0.01 to compensate for the possible increase in type I error rates that may result from multiple testing. The dichotomous measures of success and recurrence will be analysed using relative risk, and numbers needed to treat in order to provide a meaningful indicator of treatment efficacy to practitioners.

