### Primary Outcomes

#### Global perceived improvement

The participant's self-perceived level of improvement will be measured with a 6-point Likert scale with categories: completely recovered, much improved, improved, no change, worse and much worse [10,20]. The participant will be asked at each follow-up outcome assessment to rate the change in their elbow condition since their commencement in the study. A similar retrospective assessment scale has been shown to be more sensitive to change than serial visual analogue scale measures and more correlated with patient's satisfaction with change [37].

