#### Success

Success will be derived from the global perceived improvement scale as per previous work [10,20]. The categories 'completely recovered' and 'much improved' will be dichotomised as 'success', while the other categories ('much worse' to 'improved') will be collapsed to represent 'no-success'.

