#### Recurrence

Recurrence will primarily be defined as occurring when a participant rates a success at 4 or 8 weeks and a no-success beyond 8 weeks on the global perceived improvement scale [10]. This definition of recurrence which evaluates the pattern of recurrent events over time has been used in previous studies of LE [10,20,38]. In addition, participants will be questioned using a semi-structured interview at 12, 26 and 52 weeks about their experience of symptom aggravation and possible reasons for their recurrence. This data will enable better understanding of recurrences and best practice measurement of recurrence rates in future analyses and trials.

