### Randomisation and allocation

Participants will be randomly allocated to groups by concealed allocation. The Queensland Clinical Trials Centre, an independent off-site body, will be responsible for generating the computerised randomisation schedule. An independent research officer will administer the schedule and perform all communication between participants and treating practitioners. Randomisation will be stratified according to baseline pain severity, as it has been found to be a strong prognostic indicator for LE [54]. The mean VAS pain score reported in a previous clinical trial (57.5 mm) [10] will be used to classify participants into high and low baseline pain.

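### The own-baseline covariate rule cannot act on the primary outcomes, and baseline pain, the stratification factor, is not a named term in their models

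*Protocol article*

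**What the plan says.** The analysis rules are in the protocol article under Planned Data analysis, Clinical Efficacy.

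- **The one unconditional covariate rule:** "Baseline scores for each dependent variable will be entered as a covariate".
- **Other covariates:** age, gender, duration and employment, given as examples, "will be included as covariates in the analysis, if found to significantly influence outcomes over time". No test, threshold or time point is given.
- **Remaining terms:** treatment and time are fixed factors, and unnamed participant characteristics enter as a random effect.
- **Analysis alpha and summaries:** alpha is 0.01, and success and recurrence are reported as relative risk and number needed to treat.

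The primary outcomes are defined elsewhere.

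- **Global improvement:** "The participant will be asked at each follow-up outcome assessment to rate the change in their elbow condition since their commencement in the study". Table 2 marks it at follow-up visits only.
- **Success:** "Success will be derived from the global perceived improvement scale as per previous work".
- **Recurrence:** "Recurrence will primarily be defined as occurring when a participant rates a success at 4 or 8 weeks and a no-success beyond 8 weeks".

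Randomisation and allocation states: "Randomisation will be stratified according to baseline pain severity, as it has been found to be a strong prognostic indicator for LE". A VAS value of 57.5 mm "will be used to classify participants into high and low baseline pain".

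**The concern.** Two parts of the plan do not meet. The design treats baseline pain as important enough to balance on. The analysis section has one rule that always applies, and that rule finds no baseline score for any of the three primary outcomes. Baseline pain is then left without a guaranteed place in exactly the models that decide the trial.

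When arms are balanced within a prognostic stratum and the model ignores it, the standard error is larger than it needs to be. The test becomes conservative and power is lost.

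The significance screen adds a second difficulty. A logistic treatment odds ratio changes meaning with the covariates in the model, even under perfect balance. If a screen decides which covariates enter, it also decides which odds ratio is estimated.

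**Working it through.** **1. Does the own-baseline rule reach the primary outcomes?** Table 2 marks VAS pain, PRTEE, EuroQol, pain-free grip and pressure pain threshold at week 0, so the rule works for those. It does not mark global improvement at week 0, and a rating of change since entry could not have a value then. Success and recurrence derive from that rating. The rule reaches none of the three.

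**2. Could baseline pain enter another way?** The covariate list is open-ended, so it could enter there, but only if significant. It might also count as one of the unnamed participant characteristics, but those are random effects, which do not suit a two-level stratum. Neither route guarantees adjustment.

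**3. Reproduce the stated sample size.** Inputs from Sample size: 27% against 52%, alpha 0.05 (taken as two-sided), power 80%. With the mean rate (0.27 + 0.52)/2 = 0.395:

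n per margin = [1.96·√(2×0.395×0.605) + 0.8416·√(0.27×0.73 + 0.52×0.48)]² / 0.25² = (1.355 + 0.562)² / 0.0625 ≈ 58.8, so 59 per margin and 118 in total.

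The stated 120 is reproduced closely. Power at 60 against 60 is 80.8%. This point does not touch the sample size.

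**4. Approximate size of the omission.** The article gives no stratum effect, so these are assumptions. With equal strata, R² = ((p_low − p_high)/2)² / (p̄(1 − p̄)), and the actual level of an unadjusted 5% test is 2·[1 − Φ(1.96/√(1 − R²))].

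- 50% against 30% success (odds ratio 2.3): R² = 0.01/0.24 = 0.042; actual level 4.5%.
- 55% against 25% success (odds ratio 3.7): R² = 0.0225/0.24 = 0.094; actual level 4.0%.

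**5. Simulation.** Logistic regression, N = 120, two equal strata balanced by arm, marginal rates held at 27% and 52% (39.5% in both arms for type I error), 4,000 runs per row. Entries are stratum omitted → included.

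| Stratum OR (assumed) | Type I at 5% | Power, alpha 0.05 | Power, alpha 0.01 | Treatment OR given stratum |
|---|---|---|---|---|
| 1 | 4.7% → 4.8% | 81.6% → 81.7% | 60.5% → 61.0% | 2.93 |
| 2 | 4.4% → 4.6% | 81.1% → 81.6% | 58.3% → 60.6% | 3.02 |
| 4 | 3.7% → 4.7% | 83.3% → 85.8% | 59.9% → 64.5% | 3.31 |
| 8 | 2.4% → 4.6% | 83.6% → 88.2% | 58.5% → 69.0% | 3.87 |

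The Monte Carlo standard error of a single entry is about 0.3 points for type I error (√(0.05×0.95/4000)) and 0.6 to 0.8 points for power. Each pair uses the same simulated data, so the differences are more precise than that. A separate simulation over odds ratios 2.3 to 4 agreed. Type I error was 3.7% to 4.6% with the stratum omitted and about 5% with it included. Power moved from 81–82% to 81–84% at alpha 0.05, and from 58–60% to 61–64% at 0.01.

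**6. What the screen does to the target.** The last column shows the treatment odds ratio moving from 2.93 to 3.31 when a stratum with odds ratio 4 is conditioned on, although the marginal rates are unchanged. The marginal summaries do not move: relative risk 0.52/0.27 = 1.93 and number needed to treat 1/0.25 = 4. If the four named covariates were independent, unrelated to outcome and each screened at 0.05 (threshold assumed), the chance that at least one enters is 1 − 0.95⁴ = 18.5%. At 0.01 it is 1 − 0.99⁴ = 3.9%.

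**The case against.** **The baseline sentence is generic.** It applies properly to every outcome measured at week 0 and simply does not bind on a change rating. That is fair: the sentence is not wrong for the secondary outcomes. What stands is that nothing takes its place for the primary ones.

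**Naming stratification terms is detail for a statistical analysis plan.** For a bare omission this would be a good answer. Here the article also states a rule, entry on significance, which a later plan fixing the covariates would have to contradict. For the VAS outcomes the own-baseline score largely carries the stratum information, so the gap is mainly in the primary and non-pain outcomes.

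**The stratum effect is unknown.** This stands. At an odds ratio of 1 to 2 and alpha 0.05 the loss is negligible, and nothing in the article supports a value as large as 8.

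**Stronger readings that a reader might infer.**

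- *Omitting the stratum inflates false positives.* It does the opposite: the test becomes conservative.
- *Selecting covariates on significance makes the p-value too small.* This is not dependably so. Simulations with 60 against 60, no treatment effect, 4 or 8 covariates and 10,000 runs (standard error about 0.2 points) gave 4.9% to 5.4% when treatment was left out of the screening model, against 5.2% to 5.8% for a fixed set of all covariates. With treatment in the screening model the figures were 5.1% to 5.8% against 5.2% to 5.8%. A further check found selection above the fixed set only with 8 covariates screened with treatment in the model.
- *The analyst can pick the model that favours a treatment.* The same section has the analysis done by an investigator blind to allocation, and the stated criterion is influence on the outcome, not on the treatment effect. The objection to the screen is that the model and its odds ratio are not fixed in advance.

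**Conclusion.** The point holds as a modest loss of efficiency and an incompletely fixed primary model. It is not a threat to validity. For an assumed stratum odds ratio of 2 to 4, a nominal 5% test runs at about 3.7% to 4.6%. The power loss is about 0.5 to 2.5 points at alpha 0.05 (81.6 − 81.1 and 85.8 − 83.3) and about 2 to 5 points at the planned 0.01 (60.6 − 58.3 and 64.5 − 59.9). These figures assume equal, balanced strata and the article's own 27% and 52%. With a weaker stratum the loss is close to nothing.

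The roughly 59% power at alpha 0.01 should not be attributed to this point. It comes from sizing the trial at 0.05 and testing at 0.01, and would be there with or without the stratum term.

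**What to change.** - Limit the own-baseline rule to outcomes measured at week 0.
- Name baseline pain as a fixed covariate in every model for global improvement, success and recurrence, as either the continuous VAS or the high/low stratum. If continuous, say which VAS, because Randomisation and allocation does not say whether resting or worst pain is meant.
- For the non-pain secondary outcomes, such as grip force, add the stratum alongside the outcome's own baseline value.
- Replace entry on significance with a covariate set listed in advance and kept whatever its p-values. Present any further adjustment as sensitivity analysis.
- State how the planned relative risk and number needed to treat come from the adjusted analysis, since a logistic model returns a conditional odds ratio. Standardisation over the observed covariates, a log-link or modified Poisson model, or Mantel-Haenszel pooling over strata would each serve. One should be chosen in advance.

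Baseline pain is already collected, so no data collection or sample size changes. The cost is revised wording and a little extra analysis work, mostly for the relative risk and number needed to treat.

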## Abstract

**Background:**

Corticosteroid injection and physiotherapy are two commonly prescribed interventions for management of lateral epicondylalgia. Corticosteroid injections are the most clinically efficacious in the short term but are associated with high recurrence rates and delayed recovery, while physiotherapy is similar to injections at 6 weeks but with significantly lower recurrence rates. Whilst practitioners frequently recommend combining physiotherapy and injection to overcome harmful effects and improve outcomes, study of the benefits of this combination of treatments is lacking. Clinicians are also faced with the paradox that the powerful anti-inflammatory corticosteroid injections work well, albeit in the short term, for a non-inflammatory condition like lateral epicondylalgia. Surprisingly, these injections have not been rigorously tested against placebo injections. This study primarily addresses both of these issues.

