**Methods:**

A randomised placebo-controlled clinical trial with a 2 × 2 factorial design will evaluate the clinical efficacy, cost-effectiveness and recurrence rates of adding physiotherapy to an injection. In addition, the clinical efficacy and adverse effects of corticosteroid injection beyond that of a placebo saline injection will be studied. 132 participants with a diagnosis of lateral epicondylalgia will be randomly assigned by concealed allocation to one of four treatment groups – corticosteroid injection, saline injection, corticosteroid injection with physiotherapy or saline injection with physiotherapy. Physiotherapy will comprise 8 sessions of elbow manipulation and exercise over an 8 week period. Blinded follow-up assessments will be conducted at baseline, 4, 8, 12, 26 and 52 weeks after randomisation. The primary outcome will be a participant rating of global improvement, from which measures of success and recurrence will be derived. Analyses will be conducted on an intention-to-treat basis using linear mixed and logistic regression models. Healthcare costs will be collected from a societal perspective, and along with willingness-to-pay and quality of life data will facilitate cost-effectiveness and cost-benefit analyses.

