### Outcome assessment

Participants will be evaluated by a blinded assessor at baseline, 4, 8, 12, 26 and 52 weeks following randomisation. The 4 and 8 week time points will be used primarily to investigate the short term effects of corticosteroid injection compared to saline injection and of addition of physiotherapy to injection respectively. The 52 week time point will provide a primary end point for study of all long term effects. The data from the other measurement points (12–52 weeks) will be used to derive indices for recurrence rates. These time points have been chosen on the basis of a previous study which noted deterioration in the corticosteroid injected group during this time period [10].

Socio-demographic information will be collected at baseline including age, gender, employment nature, smoking status, body mass index and physical activity status. Information will be sought regarding the nature, duration and onset of LE symptoms, previous treatment and presence of concomitant neck or arm pain. The following outcome measures will be collected at baseline assessment and at follow-up evaluations as outlined in Table 2.

**Table 2 T2:** Outcome measures used at baseline and follow-up interviews

**Outcome Measures**	**Time Point (weeks)**	
	
	**0**	**4, 8, 12, 26 & 52**
Global Perceived		x
Improvement		
Resting/Worst Pain (VAS)	x	x
Pain/Disability (PRTEE)	x	x
Quality of Life (EuroQol)	x	x
Anxiety/Depression (HADS)	x	
Kinesiophobia (Tampa)	x	
Pain-free Grip Force	x	x
Pressure Pain Threshold	x	x
Adverse events		x
Willingness-to-pay	x	
Costs		4 randomly allocated time points

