### Sample size

The primary aim of this project is to detect a clinically important difference between injection alone and physiotherapy plus injection. It is estimated that 120 participants will be required to detect a 25% difference between physiotherapy and no physiotherapy (α = 0.05, β = 0.2), assuming a success rate of 27% in the least significant group. This difference is based on previous work and is clinically meaningful [20]. An extra 10% will be recruited to allow for conservative loss to follow-up, bringing the total participants to 132. The power calculation is based on previous findings that injection and physiotherapy are both effective interventions [10,20] and that the combination of the two will be additive, but not synergistic in effect.

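### The article is inconsistent about what is primary, and its flat alpha of 0.01 is tied to no defined set of tests and differs from the 0.05 used for sizing

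*Protocol article*

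**What the plan says.** **Outcome.** The Abstract (Methods) designates a single measure: "The primary outcome will be a participant rating of global improvement, from which measures of success and recurrence will be derived". The Primary Outcomes section then has three entries: the 6-point global rating, success dichotomised from it, and recurrence. For the last, "Recurrence will primarily be defined as occurring when a participant rates a success at 4 or 8 weeks and a no-success beyond 8 weeks".

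**Contrast.** The Abstract (Background) describes two gaps, the value of adding physiotherapy to an injection and the lack of placebo-controlled evidence for steroid, and says "This study primarily addresses both of these issues". Sample size gives one: "The primary aim of this project is to detect a clinically important difference between injection alone and physiotherapy plus injection". The calculation there is on a success proportion ("α = 0.05, β = 0.2), assuming a success rate of 27% in the least significant group") and names no visit.

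**Time.** Outcome assessment says "The 52 week time point will provide a primary end point for study of all long term effects". It also says "The 4 and 8 week time points will be used primarily to investigate the short term effects of corticosteroid injection compared to saline injection"; the sentence goes on to pair week 4 with the injection question and week 8 with the physiotherapy question.

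**Error rate.** Planned Data analysis, Clinical Efficacy, states: "Alpha will be set at 0.01 to compensate for the possible increase in type I error rates that may result from multiple testing". It does not say which tests the level covers or how 0.01 was chosen.

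**The concern.** Three measures derived from one scale can give different answers to the same question. If the document does not say which measure, contrast and visit decide the trial, the reading of a mixed result depends on a choice made later. Whether 0.01 is strict enough depends on how many tests share it, and the statements on what is primary support different counts. The same 0.01 also bears on the one comparison that was powered, because the sample size was derived at 0.05. The level may therefore be too strict for the sized test and, on a broad reading of what is primary, not strict enough for the whole set.

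**Working it through.** **1. Reproducing the sample size.** From Sample size: 27% in the lower group, a 25-point difference (so 52%), α = 0.05, power 80%. I assume two-sided tests and equal allocation, since neither is stated.

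n per level = [z(1−α/2)·√(2p̄q̄) + z(0.80)·√(p₁q₁ + p₂q₂)]² / d², with p̄ = (0.27 + 0.52)/2 = 0.395

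- √(2 × 0.395 × 0.605) = 0.6913
- √(0.27 × 0.73 + 0.52 × 0.48) = 0.6684
- n = (1.960 × 0.6913 + 0.842 × 0.6684)² / 0.25² = 58.8, rounded up to 59

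The total is 118, against the stated 120. So 120 fits a single comparison of success between physiotherapy levels (60 versus 60) at two-sided 0.05. Adding 10% gives 120 × 1.10 = 132.

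**2. The same comparison at 0.01.** Power = Φ{[d√n − z(1−α/2)·0.6913] / 0.6684}, with n = 60 and d√n = 1.9365.

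- α = 0.05: Φ[(1.9365 − 1.3550)/0.6684] = Φ(0.870) = 80.8%
- α = 0.01: Φ[(1.9365 − 1.7808)/0.6684] = Φ(0.233) = 59.2%

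With all 132 evaluable, power at 0.01 is 64.6%. For 80% power at 0.01, n = (1.7808 + 0.5625)²/0.0625 = 87.9, so 88 per level and 176 in total (176/0.90 gives 196 with 10% loss).

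**3. Familywise error at 0.01 per test.** For m independent tests it is 1 − 0.99^m; the Bonferroni bound is 0.01m. Correlated tests were simulated under the global null: 6,000 trials per setting, 120 participants in a 2 × 2 factorial, within-person correlation 0.3, 0.5 and 0.7, and an assumed 40% success rate. The rating was compared by t-test, and success and recurrence by two-proportion tests.

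| Tests counted | m | Independent | Simulated |
|---|---|---|---|
| Physiotherapy: rating and success at week 52, recurrence | 3 | 3.0% | 2.4–2.7% |
| Success at week 52 and recurrence, both contrasts | 4 | 3.9% | 3.9–4.1% |
| Any five tests | 5 | 4.9% (bound 5.0%) | not run |
| Three outcomes × two contrasts, week 52 | 6 | 5.9% | 5.1–5.4% |
| Those six, plus rating and success for injection at week 4 and physiotherapy at week 8 | 10 | 9.6% | 7.6–8.5% |
| Rating and success at all five visits, both contrasts, plus recurrence for each | 22 | 19.8% | 13.6–16.4% |

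The Monte Carlo standard error near 5.3% is √(0.053 × 0.947/6000) = 0.3 points, so the six-test result is best read as about 5%. A separate simulation with 20,000 trials per setting gave 5.2–5.4% for six tests and 7.6–8.2% for ten.

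**The case against.** The strongest reply is that the hypotheses at the end of Background already bound the confirmatory set. The first concerns long-term efficacy and recurrence with physiotherapy (rating and success at week 52, recurrence: three tests). The second claims steroid superiority in the short term only (rating and success at week 4: two tests). Five tests at 0.01 have a bound of exactly 5.0%. This is a fair reading and 0.01 controls it. But the article does not state that derivation, and its other sections point to different sets.

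A reader might infer four stronger things that the text does not support:

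- *There is no hierarchy.* Sample size states a primary aim and powers only that. The Abstract (Methods) and the Conclusion bring in the placebo comparison as an addition, and secondary measures have their own section. The hierarchy is inconsistent, not absent.
- *Several time points are primary.* Only week 52 is called a primary end point. For weeks 4 and 8 the adverb can mean no more than mainly.
- *A positive trial may be claimed from whichever test succeeds.* The article gives no such rule, and an analysis plan that is not shown may set the order of testing.
- *The error rate is several times what was promised.* The 0.01 is a tightened per-test level, not a promised familywise rate. The 22-test figure treats each visit as a separate primary test, although the planned models carry time as a factor.

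What remains is not missing detail that an analysis plan would supply. This document makes conflicting statements about what is primary, and it fixes an alpha that disagrees with its own sample size.

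**Conclusion.** The point holds as an inconsistency that should be corrected. The designation of the primary outcome differs between the Abstract and Primary Outcomes, and that of the primary contrast between the Abstract and Sample size. The sized comparison has no stated visit.

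Whether 0.01 suffices depends on an undefined set of tests. It suffices for up to five, including the physiotherapy contrast alone; it is borderline at about 5% for six; it is exceeded at about 8% for ten. The clear excess depends on counting the short-term tests as primary. The simulated rates rest on the assumed success rate, correlations and simple tests in place of the planned regression models.

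The alpha mismatch does not depend on that count. If the 0.01 applies to the sized comparison, power is about 59% where 80% was intended, given two-sided tests, equal allocation and 120 evaluable participants.

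**What to change.** Name one primary test: success at week 52, physiotherapy versus no physiotherapy (factorial main effect), at the two-sided 0.05 used for sizing. Describe the 6-point rating as a supportive analysis of the same outcome. List recurrence and the short-term steroid-versus-saline comparison as key secondary, with a stated multiplicity rule over that defined set, for example Holm. Treat other visits and measures as secondary or exploratory.

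State also whether the key secondary set has its own 0.05 or is tested only after a positive primary result. With its own 0.05, the bound over primary and key secondary together is 0.05 + 0.05 = 10%. That can be defended when a factorial trial asks separate questions, and making the steroid question wait on physiotherapy is a debatable preference, so the choice should be explicit.

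Use the same wording in the Abstract (Background and Methods), Outcome assessment, Primary Outcomes, Sample size and Planned Data analysis. The cost is wording only, fixed before unblinding, with no new participants or data; the planned 120 still gives 80.8% power. The downside is that recurrence and the injection contrast are no longer called primary.
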